### Criteria for discontinuing or modifying allocated interventions {11b}

Participants may be discontinued from the study if they withdraw their consent, lose interest, or are unwilling to continue. Participation will be interrupted for individuals allocated to any group in case of safety concerns, such as medical advice, complications arising from the disease, or a severe health event that precludes attendance at intervention sessions.

### Strategies to improve adherence to interventions {11c}

Participants allocated to the active control group receive text messages 2 days before the health education session to reinforce the date and time of the meeting. The exercise training groups receive messages at the beginning of each week, reinforcing the interventions’ date, time, and location. We use phone calls or WhatsApp messages to inquire about adverse events in cases where a participant misses a session from any intervention group. The call schedule is interrupted for participants who declare their withdrawal from the study.

### Relevant concomitant care permitted or prohibited during the trial {11d}

Participants were instructed not to engage in any other type of activity involving exercise during the study period. Participants were also advised to maintain usual care treatment for breast cancer, if applicable, or another coexisting disease.

### Provisions for post-trial care {30}

All participants interested in continuing physical exercises practice after the study’s conclusion will be invited to join the Exercise Research in Cancer (ERICA) Extension Project conducted in the ESEF/UFPel. This project offers a free supervised physical exercise program consisting of two sessions of 1-h per week, including aerobic and resistance exercises. This program is available to all breast cancer survivors who participated in studies associated with our laboratory.

### Outcomes {12}

The primary outcome of the study is cancer-related fatigue, measured before and after 12 weeks of intervention, using the Piper Fatigue Scale (PFS). Data are presented as group means at baseline and post-intervention time points in the assessment. Cancer-related fatigue was chosen as the primary outcome because it is one of the main complaints among breast cancer survivors [11, 12].

A set of clinically relevant secondary outcomes for breast cancer survivors was established, considering the side effects of cancer and its treatment. The secondary outcomes are measured before and after 12 weeks of intervention, presented as group means at baseline and post-intervention time points in the measurements, and include:Cardiorespiratory fitness: determined by peak oxygen consumption (VO_2peak_) and ventilatory thresholds (i.e., oxygen uptake in the first ventilatory threshold—VO_2VT1_ and oxygen uptake in the second ventilatory threshold—VO_2VT2_) obtained by an incremental test on a treadmill.Muscular performance: determined by the maximum dynamic muscular strength and dynamic muscular endurance of the knee extensors.Muscle morphology: determined by muscle thickness and muscle quality of the quadriceps femoris, measured from images obtained by B-mode ultrasonography.Functional performance: determined by functional tests performed according to the procedures proposed by Rikli and Jones [40].Mental health: measured by depressive and anxiety symptoms using the Hospital Anxiety and Depression Scale (HADS).Cognitive function: determined by aspects of perceived cognitive function measured using the Functional Assessment of Cancer Therapy—Cognitive Function—Version 3 (FACT-Cog-v3) questionnaire and aspects of objective cognitive function measured by the Trail Making Test (TMT) and the Controlled Oral Word Association Test (COWAT).Pain: measured by the Brief Pain Inventory (BPI).Quality of life: measured by the Functional Assessment of Breast Cancer Therapy (FACT-B) instrument.

### Participant timeline {13}

The schedule of trial enrollment, interventions, and assessments are presented in Table 3.

**Table 3 Tab3:** Time scheme for study conduction

	Study period							
	Enrollment	Baseline measures		Allocation	Post-allocation		Close out	
Timepoint	T-1	T0^a^		T1	T2	T3^b^	T4^ab^	
Timepoint description		Evaluation visit 1	Evaluation visit 2		Intervention start	Intervention end	Final evaluation visit 1	Final evaluation visit 2
Enrollment								
Eligibility screening	✕							
Informed consent	✕							
Allocation				✕				
Interventions								
Aquatic training program plus health education					✕	✕		
Land training program plus health education					✕	✕		
Health education program					✕	✕		
Assessments								
Primary outcome								
Cancer-related fatigue questionnaire		✕					✕	
Secondary outcomes								
Cardiorespiratory fitness			✕					✕
Maximal dynamic strength		✕					✕	
Dynamic muscular endurance		✕					✕	
Functional tests		✕					✕	
Muscle thickness and muscle quality			✕					✕
Depression and anxiety scale		✕					✕	
Cognitive function questionnaire and tests		✕	✕				✕	✕
Pain inventory			✕					✕
Quality of life questionnaire		✕					✕	
Additional measurements								
Anthropometric measurements			✕					✕
Physical activity levels			✕					✕
Food consumption			✕					✕
Office blood pressure			✕					✕
Follow-up questionnaire								✕

^a^period will be no longer than 2 weeks

^b^time between t3 and t4 will be no longer than 2 weeks

### Sample size {14}

The sample calculation was conducted using the GPower version 3.1 program, adopting a significance level of *α* = 0.05 and 90% power. Data for the calculation were derived from the study results by Kessels et al. [12] for the primary outcome of cancer-related fatigue (effect size 0.605). It resulted in a total sample size of 39 subjects. Additionally, nine individuals (approximately 20%) will be included in the study to account for potential sample losses, totaling 48 participants randomized into the three groups.

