## Introduction

### Background and rationale {6a}

Breast cancer stands as the most prevalent cancer type among women worldwide. In 2022, it accounted for approximately 2.3 million new diagnoses, representing 23.8% of all new cases in women and the most frequent cause of death (666,103 deaths) across all age groups [1]. In Brazil, excluding non-melanoma skin tumors, it is the most incident cancer among women across all regions of the country. Projections for 2023 to 2025 estimate 73,610 new breast cancer cases in Brazil, corresponding to a risk of 66.54 new cases per 100,000 women [2].

Scientific evidence has confirmed that cancer treatment enhances survival rates [3]. However, survival is often accompanied by physical and psychological side effects caused by both the disease and the toxicity of the treatment. Persistent symptoms include exacerbated cancer-related fatigue, impaired quality of life, increased depressive and anxiety symptoms, and compromised ability to perform daily activities [4–10]. Notably, cancer-related fatigue is reported as one of the most substantial challenges faced by breast cancer survivors [11, 12], with a consequent negative impact on the health-related quality of life, underscoring the paramount importance of investigating this outcome within this population.

In this context, physical exercise is considered a non-pharmacological approach to improving health-related outcomes for cancer survivors [13]. Meta-analyses of several controlled intervention studies have demonstrated that physical exercise programs can improve cancer-related fatigue, physical fitness, and mental health in this population [11, 12, 14]. While evidence supporting the positive effects of exercise programs during and after breast cancer treatment has predominantly focused on land-based exercise programs (i.e., walking/running, cycling, resistance training) [15], there is growing interest in the potential benefits of water-based exercise programs for this population [16–19]. While original evidence is increasing in this area [20–29], there is a notable lack of studies comparing the effects of exercise programs in aquatic and land environments for breast cancer survivors [24, 26].

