### Objectives {7}

We aim to analyze the effects of 12 weeks of land- or water-based exercise programs compared with a health education program alone on cancer-related fatigue, cardiorespiratory fitness, muscular performance, muscle morphology, functional performance, mental health, cognitive function, pain, and quality of life in breast cancer survivors. Herein, we report the protocol of the WaterMama Study, a superiority randomized clinical trial with three parallel groups, using cancer-related fatigue as the primary outcome. Based on the intervention design and outcomes of interest, we hypothesize that both training programs will significantly improve the investigated outcomes compared to the health education group alone. Additionally, we expect the water-based exercise program to have a more significant positive impact on cancer-related fatigue and physical parameters due to its multi-component nature.

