## Statistical methods

### Statistical methods for primary and secondary outcomes {20a}

We will use descriptive statistics, including mean, standard deviation, 95% confidence intervals, and absolute or relative frequencies as applicable. The Shapiro–Wilk and Levene tests will be used to assess data normality and homogeneity. Generalized estimating equations, with Bonferroni adjustment for post hoc tests, will be used to compare time points and groups. One-way ANOVA and/or Kruskal–Wallis tests will be conducted to compare training compliance and follow-up questionnaire responses between groups. Effect sizes between groups will be calculated based on the absolute difference (± SD) between baseline and post-intervention values, using Cohen’s *d*. All statistics procedures will be performed in the SPSS vs. 28.0, with a significance level set at *α* = 0.05.

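### The 90% power at N=39 belongs to an overall F test; it does not cover the Bonferroni-adjusted pairwise comparisons that the hypotheses need, whose power is well below 90% if 0.605 is a two-arm difference

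*Protocol article*

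**What the plan says.** Sample size {14} reports a calculation in G*Power 3.1, "adopting a significance level of *α* = 0.05 and 90% power". The input comes from a cited study, "for the primary outcome of cancer-related fatigue (effect size 0.605). It resulted in a total sample size of 39 subjects". Nine more participants for losses bring the total to 48, or 16 per arm under 1:1:1 allocation. The section does not say whether 0.605 is Cohen's f, Cohen's d or another measure, which test was chosen, or what pre-post correlation was assumed.

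The source of 0.605 is also cited in Background and rationale {6a}, in support of the sentence "Meta-analyses of several controlled intervention studies have demonstrated that physical exercise programs can improve cancer-related fatigue".

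Objectives {7} hypothesises that each exercise programme improves outcomes over health education alone, and adds: "we expect the water-based exercise program to have a more significant positive impact on cancer-related fatigue and physical parameters due to its multi-component nature". These are three pairwise questions.

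Statistical methods {20a} plans: "Generalized estimating equations, with Bonferroni adjustment for post hoc tests, will be used to compare time points and groups". No power is given for any pair.

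**The concern.** A reader of the sample-size section will take the trial to have 90% power for its primary question on fatigue. That question is pairwise: does each programme beat education, and does water beat land? A significant overall test cannot answer it, because it does not say which arms differ. If the 90% was computed for an overall test, it does not describe the comparisons on which the conclusions will rest.

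The size of 0.605 adds to this. An effect drawn from controlled exercise studies is most naturally a difference between two arms. A spread of 0.605 SD across three arm means is a much larger effect. A non-significant contrast could then be read as coming from a well-powered test when it does not.

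**Working it through.** **Inputs.** From the protocol: alpha 0.05, power 0.90, effect size 0.605, N=39 (13 per arm), N=48 (16 per arm), three arms, two time points. Assumed here: Bonferroni over the three between-group pairs (alpha 0.05/3 = 0.0167 each, two-sided) and a pre-post correlation ρ from 0 to 0.8, since neither is stated.

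**1. Reproducing 39.**
- One-way ANOVA, three groups, f = 0.605: noncentrality λ = f²N = 0.366N. Power is 0.893 at N=37, 0.902 at N=38 and 0.910 at N=39. The first size with equal arms is 39.
- Group-by-time interaction, f = 0.605/2 = 0.3025, ρ = 0.5: λ = f²N·2/(1−ρ) = 0.0915 × 4 × N = 0.366N, with the same degrees of freedom (2 and N−3). Power is identical, so again 39.
- A between-group repeated-measures F test with f = 0.605 also reaches 39, but only at ρ about 0.9.
- Routes that do not give 39: two-sample t with d = 0.605 (59 per arm two-sided, 48 one-sided); paired t (31 two-sided, 25 one-sided); one-way ANOVA with f = 0.3025 (144 in total); interaction with f = 0.605 and ρ = 0.5 (15 in total).

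**2. What the first two routes assume.** In both, the three arm means (or mean changes) have a standard deviation of 0.605 SD.
- Both programmes equally better than education: gap = 0.605 × 3/√2 = 1.28 SD, with water minus land equal to zero.
- Equally spaced arms: extremes 0.605 × √6 = 1.48 SD apart, neighbours 0.74 SD apart.

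**3. Overall power if 0.605 is a two-arm difference.** If both programmes exceed education by 0.605 SD, then f = 0.605 × √2/3 = 0.285. This gives λ = 0.0813 × 39 = 3.17 and power 31% at N=39; λ = 3.90 and power 38% at N=48. The interaction test at ρ = 0.5 gives the same values. A higher ρ would raise them.

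**4. Pairwise power at a 0.605 SD difference, alpha 0.0167.** Noncentral t with δ = d√(n/2). Without gain from baseline, δ = 0.605 × √6.5 = 1.54 at 13 per arm and 0.605 × √8 = 1.71 at 16, against critical values of about 2.57 and 2.54. Baseline adjustment replaces d by d/√(1−ρ²), which is 0.699, 0.847 and 1.008 at ρ = 0.5, 0.7 and 0.8. A comparison of changes replaces it by d/√(2(1−ρ)).

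| Analysis (ρ assumed) | 13 per arm | 16 per arm |
|---|---|---|
| No baseline gain, or change at ρ 0.5 | 17% | 22% |
| Baseline-adjusted, ρ 0.5 | 24% | 30% |
| Change, ρ 0.7 | 30% | 39% |
| Baseline-adjusted, ρ 0.7 | 36% | 45% |
| Change, ρ 0.8 | 46% | 57% |
| Baseline-adjusted, ρ 0.8 | 51% | 62% |

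Baseline-adjusted rows spend one degree of freedom on the covariate; other conventions for the error degrees of freedom move them by two points at most. For 90% power per pair, about 76 per arm are needed without baseline gain, 57 with adjustment at ρ 0.5, and 40 at ρ 0.7.

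**5. Pairwise power if 0.605 is truly f, alpha 0.0167, no baseline gain.**

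| Contrast | 13 per arm | 16 per arm |
|---|---|---|
| Either programme vs education, 1.28 SD | 75% | 86% |
| Extreme arms, 1.48 SD | 88% | 94% |
| Adjacent arms, 0.74 SD | 27% | 35% |

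**6. Detectable difference.** Solving the same formula for 90% power at 13 per arm gives about 1.5 SD without baseline gain. Baseline adjustment multiplies this by √(1−ρ²): about 1.3 SD at ρ 0.5 and 1.1 SD at ρ 0.7.

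**The case against.** The strongest defence has four parts.

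- **The article does not say how 0.605 was used.** A reader might infer that a Cohen's d was mistakenly entered as Cohen's f in a one-way ANOVA. The document does not support that as fact. The interaction route gives the same 39, treats 0.605 as a d that has been halved, and fits the planned time-by-group model better. The sample-size section says the data were derived from the source's results, which leaves room for a conversion, and the source is not at hand. This stands. It does not rescue the pairwise power, because at ρ 0.5 the interaction route also implies a 1.28 SD gap in change.
- **A condensed article may leave metric, test and correlation to the full protocol.** This stands, so their absence alone is not the point. The point is a definite 90% attached to the primary outcome beside hypotheses that it does not cover.
- **The Bonferroni tests are post hoc to the GEE model, and sizing a three-arm trial on the model-level test is legitimate.** This stands in part. The overall test is one of the planned tests, and 90% can be true of it. The stated hypotheses, however, are decided by the contrasts.
- **Not every contrast falls short.** A reader might infer that every hypothesis is underpowered. If 0.605 is f and the means are equally spaced, the extreme arms (water versus education, in the hypothesised order) have 88% power at 13 per arm and 94% at 16. This stands, and so no single range of pairwise power should be quoted without its assumptions.

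The plan is a superiority trial with confidence intervals and Cohen's d, and announces no equivalence claim. Misreading a null result is a risk for readers, not something that the plan itself does.

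**Conclusion.** The point holds in this form: the 90% at N=39 matches an overall F test that assumes a 0.605 SD spread across three arms, and it does not apply to the pairwise hypotheses.

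If 0.605 is an exercise-versus-control standardised difference, adjusted pairwise power is between 17% (13 per arm, no baseline gain) and 62% (16 per arm, baseline-adjusted, assumed ρ 0.8), and overall power is 31% at N=39 and 38% at N=48 on a single score or at ρ 0.5. That reading is likely, because the source is cited among meta-analyses of controlled studies, but the document does not prove it.

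If 0.605 is truly f, the 90% is right for the overall test. The water-versus-land comparison is then either assumed to be zero or, with equally spaced means, has 27% to 35% power.

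The percentages rest on three Bonferroni pairs and the stated values of ρ. How 0.605 was entered into the software remains unknown.

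**What to change.** Keep N=48 and rewrite the sample-size paragraph:

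- Name the metric of 0.605, the test used in G*Power and any correlation assumed.
- If 0.605 is f, limit the 90% to the overall test and state the pattern of means it assumes. If it is a two-arm difference, withdraw the 90%.
- Report the power at a 0.605 SD difference and the difference detectable with 90% power for each Bonferroni-adjusted contrast: about 1.5 SD at 13 per arm without baseline gain, and smaller with baseline adjustment at a stated assumed correlation.
- State that water versus land is not powered and will be reported as an estimate with a confidence interval.

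The cost is one reworded paragraph and a matching registry update. No participants are added. The downside is that the stated power becomes less favourable.

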### Recruitment {15}

The recruitment period began in January 2023 and is expected to conclude by August 2024. Upon authorization from the Head of the Oncology Service at Hospital Escola/UFPel and Santa Casa de Misericórdia de Pelotas, lists of service users’ telephone numbers are compiled from the corresponding medical records departments. These individuals are then contacted by phone and WhatsApp messages and invited to participate in the study. Additionally, the study is promoted through announcements in local or regional newspapers and on social media, including the contact information for interested individuals. During the phone contact, individuals receive comprehensive information about the study’s purpose and undergo a screening to determine their eligibility based on inclusion criteria.

The potential eligible participants are then invited to visit the LabNeuro at ESEF/UFPel for an individual interview with one of the responsible researchers ([name] or [name]). During this initial visit, detailed information about the research procedures, including questions regarding the exclusion criteria, is provided. Eligible participants are fully informed about all procedures, including potential risks and benefits, and are asked to sign an informed consent form if they agree to participate.

## Assignment of interventions: allocation

### Sequence generation {16a}

The randomization sequence is generated on the website www.random.org, with a 1:1:1 proportion and stratification by endocrine therapy (aromatase inhibitors, selective estrogen receptor modulators, and no endocrine therapy). The sequence is based on randomly sized blocks that are not disclosed to ensure concealment.

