An important characteristic of the aquatic environment is the lower apparent weight resulting from water immersion, corresponding to around 20 to 30% of the total body weight on land in women with different age ranges and body compositions [30, 31]. This substantially reduced load to be supported during water-based exercises facilitates exercise performance and reduces osteoarticular impact. Additionally, the physical properties of the aquatic environment provide analgesic effects in a pleasant setting [20], promoting well-being and favoring adherence to exercise programs. The large sensory flow in water may be responsible for reduced pain perception, with pain modulation affected by factors such as water temperature and turbulence (therapeutic effect of hydromassage) [32]. This aspect may be particularly beneficial for breast cancer survivors undergoing hormonal therapy, as joint pain and other musculoskeletal disorders may arise as possible adverse effects [33].

Moreover, water-based exercises may offer advantages due to their multi-component nature. A program involving aerobic exercises performed in water can yield improvements not only in cardiorespiratory parameters but also in flexibility, balance, and muscle strength, thickness, and quality [34–36]. These characteristics may be attributed to the water’s physical properties, such as drag force and buoyancy, which provide a multidirectional resistance and a higher instability than the land environment during exercise performance [37]. Although such outcomes were primarily investigated in older populations, it is plausible that these findings may be applicable to breast cancer survivors. Considering the physical and psychological impairments in breast cancer survivors, it is pertinent to investigate if exercise programs performed in the aquatic environment may potentiate health-related benefits.

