### Methods in analysis to handle protocol non-adherence and any statistical methods to handle missing data {20c}

The primary and secondary outcomes will be analyzed according to intention-to-treat (ITT) principles, which include all randomized participants. Missing data will be handled by multiple imputations using generalized estimation equations. Additionally, a per-protocol (PP) analysis will be conducted, including only the participants who completed the trial (completers) with adherence to at least 70% of the intervention sessions.

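### Randomisation is stratified by endocrine therapy, but the stated analysis names only time points and groups, so some precision may be forgone

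*Protocol article*

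**What the plan says.** Sequence generation {16a} sets out allocation "with a 1:1:1 proportion" and "stratification by endocrine therapy (aromatase inhibitors, selective estrogen receptor modulators, and no endocrine therapy". On blocking it says: "The sequence is based on randomly sized blocks that are not disclosed to ensure concealment".

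Statistical methods {20a} gives the model for primary and secondary outcomes: "Generalized estimating equations, with Bonferroni adjustment for post hoc tests, will be used to compare time points and groups". No covariate or stratum term is named. Section {20b} plans no additional analyses. Section {20c} says: "The primary and secondary outcomes will be analyzed according to intention-to-treat (ITT) principles, which include all randomized participants". It adds multiple imputation and a per-protocol analysis, again without the stratum.

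The Background {6a} gives one reason why endocrine therapy may matter in this trial. On the analgesic effect of water it says: "This aspect may be particularly beneficial for breast cancer survivors undergoing hormonal therapy, as joint pain and other musculoskeletal disorders may arise".

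**The concern.** Stratified blocks balance the arms within each endocrine-therapy group. If that factor is related to the outcome, the balance makes the difference between arms less variable than simple randomisation would. A model that omits the factor leaves the between-stratum variation in its residual, so it reports a standard error for the less precise design. Intervals are then too wide and tests reject too rarely under the null.

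At stake is efficiency in a trial of 48 women, about 16 per arm, whose hypotheses are pairwise (each exercise arm against education, and water against land) and whose post hoc tests already carry a Bonferroni adjustment. Pain, function and quality of life are among the secondary outcomes, and endocrine therapy could plausibly matter for them.

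**Working it through.** **1. The plan's own figure.** Sample size {14} uses alpha 0.05, 90% power and "effect size 0.605", and concludes: "It resulted in a total sample size of 39 subjects". The article does not state the effect-size metric. Read as Cohen's f in a one-way comparison of three groups, the noncentrality at N = 39 is 0.605² × 39 = 14.27 with 2 and 36 degrees of freedom, and power is 0.910. At N = 36 it is 0.883, so 39 is reproduced, without any stratum term. At N = 48 power is 0.961.

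**2. Size of the standard-error error.** Let R² be the share of variance of the compared quantity that the stratum explains. The documents do not give it; 0 to 0.30 is assumed. With near-complete balance within strata, the unadjusted standard error is too large by 1/√(1 − R²), and a nominal two-sided 5% test has a true level of about 2 × [1 − Φ(1.96/√(1 − R²))].

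- R² = 0.10: factor 1.05; 1.96 × 1.054 = 2.07; level about 3.9%
- R² = 0.20: factor 1.12; 1.96 × 1.118 = 2.19; level about 2.8%
- R² = 0.30: factor 1.20; 1.96 × 1.195 = 2.34; level about 1.9%

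**3. Simulation of the three-group test.** 6,000 trials per setting; blocks of 3 or 6 within strata; stratum shares 40/35/25% (assumed); a single analysed value per woman; power at f = 0.605.

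| N | R² | Type I, without stratum | Type I, with stratum | Power, without | Power, with |
|---|---|---|---|---|---|
| 39 | 0 | 0.048 | 0.048 | 0.914 | 0.910 |
| 39 | 0.10 | 0.037 | 0.049 | 0.915 | 0.936 |
| 39 | 0.20 | 0.025 | 0.049 | 0.928 | 0.962 |
| 39 | 0.30 | 0.017 | 0.050 | 0.935 | 0.979 |
| 48 | 0 | 0.046 | 0.046 | 0.960 | 0.959 |
| 48 | 0.10 | 0.042 | 0.055 | 0.968 | 0.976 |
| 48 | 0.20 | 0.023 | 0.048 | 0.972 | 0.988 |
| 48 | 0.30 | 0.016 | 0.049 | 0.976 | 0.993 |

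The power forgone is 0 to about 4 points at N = 39 and 0 to about 2 at N = 48.

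**4. Pairwise power.** For an assumed difference of 1 SD at N = 48 (4,000 trials per setting), power without and with the stratum is 79.6% and 79.5% at R² = 0, 79.5% and 82.7% at 0.10, 81.9% and 87.6% at 0.20, and 82.1% and 90.1% at 0.30. The gain from adjusting is therefore 0 to 8 points.

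**5. Which contrast is affected.** There are two time points. Write the outcome as Y = (stratum level) + (group, time and person terms). If the stratum level is the same at both times, it drops out of each woman's change and hence out of the time-by-group contrast. Pairwise type I error at N = 48, unadjusted:

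- Group comparison of the post-intervention value: about 3.4% at R² = 0.10, falling to about 1.9% at 0.30.
- Change, where the stratum shifts only the level: 4.4% to 5.7% across runs and settings, so no conservatism.
- Change, where the stratum predicts change: 4.0% to 4.2% at 10% of change variance, 2.7% to 3.2% at 20%, and 2.1% at 30%.

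**6. What adding the stratum does in the GEE.** One complete simulated data set, N = 48, with a stable stratum difference. The two time-by-group standard errors were 0.345 and 0.304 without the stratum, exactly the same with a stratum main effect, and 0.344 and 0.305 with stratum-by-time. The main effect did reduce the standard errors of the baseline group differences, from 0.522 and 0.439 to 0.324 and 0.379. A main effect thus helps a comparison of levels but does nothing for the time-by-group contrast.

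**The case against.** The strongest reply is that {20a} is a single condensed sentence. It says what will be compared; it neither lists nor excludes covariates, and a fuller protocol or analysis plan may contain the stratum. This stands in part. A reader might infer that the model has only time and group and that the factor was deliberately dropped, but the text does not say so. What remains is that the article states its design factor and its primary method, and the two do not connect anywhere in the statistical sections.

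A second reply is that no conservatism arises on change if endocrine therapy shifts fatigue equally at both times. That is correct (step 5) and limits the point to post-intervention comparisons and to strata that predict change. The article does not say which contrast carries the primary conclusion.

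Third, GEE with an uncorrected sandwich variance is itself somewhat liberal at about 16 per arm: 6.5% in simulation with no stratum effect, and 5.6% when the stratum explains 10% of change variance. The net level therefore depends on a variance estimator that the article does not name. This too stands, but that excess comes from the estimator, not from leaving out the stratum.

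Finally, {16a} gives no reason for stratifying, and the Background links hormonal therapy to joint pain and musculoskeletal disorders, not to fatigue. That the team regards the factor as prognostic for the primary outcome is an inference.

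**Conclusion.** The point holds as a modest matter of efficiency. To the extent that endocrine therapy predicts the post-intervention level or the change, the unadjusted comparison has too large a standard error: by about 5% to 20% for an assumed R² of 0.10 to 0.30, with a pairwise test level of roughly 4% to 2% in place of 5%. The power forgone at N = 48 is 0 to about 2 points for the three-group test and 0 to about 8 for a pairwise difference of 1 SD. Every one of these figures rests on an R² that the documents do not supply, and on assumed stratum shares and block sizes.

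A reader might go further and conclude that power is lost outright, that the planned 90% is not met, or that the error rate is unsafe. The documents do not support this. At R² = 0 nothing is lost, the figure of 39 is reproduced without any stratum term, and the omission makes tests conservative rather than liberal.

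**What to change.** In Statistical methods {20a}, state that the three-level endocrine-therapy stratum enters the primary and secondary models in a form that acts on the between-group contrast. Either of two forms serves:

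- a stratum-by-time term in the GEE, together with the stratum main effect; or
- the stratum as a covariate in a baseline-adjusted model of the week-13 value.

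In {20c}, state that the stratum is also in the multiple-imputation model. Make the change before the unblinded analysis.

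The cost is one sentence and two to four degrees of freedom: two for the stratum, and two more if it interacts with time. If the stratum proves irrelevant the price is negligible; in step 3, at R² = 0, simulated power moves from 0.914 to 0.910 at N = 39 and from 0.960 to 0.959 at N = 48.
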